**Page 3: demographics**
Gender (multiple-choice questions with only 1 acceptable answer)Age (free text with regular expression [regex] validation rule)Position (multiple-choice questions with only 1 acceptable answer; custom answer accepted)Years since graduation (free text with regular expression [regex] validation rule)Years of practice in anesthesiology (free text with regular expression [regex] validation rule)Specialist diplomas (custom answer accepted; multiple-answer question with more than 1 answer accepted)

After completing the vignettes, the participants allocated to the LoAD Calc group will be asked to complete the French version of the System Usability Scale [18], the translation of which has been validated [19]. Participants allocated to the control group will then be asked which methods they used to calculate LA doses.

Finally, both groups will have to answer a question based on a 10-point Likert scale to assess their confidence as to the method they used to carry out the maximum safe LA dose calculations, from score 1 (absolutely not confident) to score 10 (perfectly confident).

The whole study sequence is summarized in Figure 1.

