### Objectives

This study protocol follows the hypothesis that LoAD Calc, an mHealth app designed to help clinicians calculate maximum safe LA doses, is safer and more effective than traditional methods. Thus, the primary objective will be to evaluate the effectiveness of the LoAD Calc app by using it to compute the maximum single doses of LA in written simulated cases. The secondary objective will be to determine whether physicians find this app easier, faster, and safer than the methods they generally use.

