### Outcomes

The primary outcome will be the overall overdose rate, according to the method used. To assess this outcome, the maximum acceptable dose in milligrams, or milliliters, must therefore be established. While this might seem straightforward at first sight, it is actually rather complex. Indeed, although maximum safe doses are calculated in milligrams, anesthetists administer a volume of LA (the concentration of which can vary) rather than a quantity of LA. Therefore, even though toxicity is related to the quantity (in milligrams) of LA administered, it is clinically more relevant to determine the maximum volume (in milliliters) of LA that can be used for a particular patient. Consequently, after applying the rules described in Textbox 1, a quantity in milligrams will be obtained. It will then be converted in milliliters according to the concentration of the LA used in the vignette. This volume will then be rounded to the inferior integer. To be less conservative, 1 mm will be added to this calculated volume, and the total will represent the maximum acceptable volume. An overdose will be considered any dose higher than this maximum acceptable volume or than its corresponding LA quantity in milligrams.

The secondary outcomes will be the overall overdose rate, considering the simulated patient’s ideal weight and the simulated patient’s actual weight, the overdose rate according to each LA studied, and the overall underdose rate. An underdose will be defined as the maximum acceptable volume minus 20% (or its corresponding LA quantity in milligrams), rounded to the inferior integer. This is an empirical choice since anesthetic underdose can only be determined clinically [20,21].

Other secondary outcomes will be the time taken to complete these calculations, the app’s usability, and the physicians’ confidence in using the method they were allocated to. The app’s usability will be evaluated using the System Usability Scale [18]. Provided that the statistical assumptions are met, factors associated with a higher probability of overdose or underdose will also be assessed.

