### Statistical Analysis

The sample size calculation and all other statistical analyses will be carried out using Stata (version 17.0 or above). The complete data set will be exported by the webmaster, who will give the study groups codenames before sending the curated data set for statistical analysis. Descriptive statistics will be used to present demographical data. Normality will be assessed graphically, and the Kolmogorov-Smirnov test will be used in cases of doubt. Accordingly, all outcomes will then be computed using either parametric or nonparametric tests. The data acquisition mechanisms will ensure that all data are recorded after each stage. Thus, there should not be any missing data, and there shall be no need for imputation. When LA mixtures are used, participants will be told that 1 anesthetic has already been injected and the dose used has been clearly reported. Thus, they will be asked to determine the maximum safe dose for the second local anesthetic. Multivariable regression will be used to determine an association between specific clinical parameters and the probability of overdose or underdose, provided that all required assumptions are met and that the risk of overfitting is adequately limited. Double-sided *P* values (*P*<.05) will be considered significant.

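### The confidence rating follows a different questionnaire in each arm, so any question-order effect would be fully confounded with allocation

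*Protocol article*

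**What the plan says.** The order is set in Methods, Consent and Study Sequence, in the text after the box describing the first questionnaire. Once the vignettes are done, "the participants allocated to the LoAD Calc group will be asked to complete the French version of the System Usability Scale". For the other arm, "Participants allocated to the control group will then be asked which methods they used to calculate LA doses". The shared item comes last: "Finally, both groups will have to answer a question based on a 10-point Likert scale to assess their confidence as to the method they used", scored from 1 to 10.

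The Outcomes section lists "the physicians’ confidence in using the method they were allocated to" among the other secondary outcomes. The Objectives section states the secondary objective as a comparison of perceptions: to "determine whether physicians find this app easier, faster, and safer than the methods they generally use". No test is named for confidence. Statistical Analysis says in general that "all outcomes will then be computed using either parametric or nonparametric tests" and that "Double-sided *P* values (*P*<.05) will be considered significant".

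**The concern.** A rating can depend on what the respondent was asked just before it. Here one arm has just given a set of evaluative ratings of its tool, and the other has just answered a factual question about its own methods. The context of the confidence rating therefore differs by arm for a reason unrelated to how well either method served the participant.

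At stake is the interpretation of one secondary outcome. The System Usability Scale has no control-arm value, and calculation time is measured, not rated. That leaves the single confidence item as the only between-arm evidence on how physicians regard their method, which is what the secondary objective asks about.

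**Working it through.** There is no figure in the plan to reproduce for this outcome. Its sample size of 46 (23 per group, difference 10%, SD 10%, power 90%) does reproduce with a two-sided two-sample t-test: 22.02 per group, rounded up to 23, and 2 × 23 = 46. It concerns the primary outcome and has no bearing here. The check is therefore one of structure.

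1. **Order by arm (Consent and Study Sequence).**
   - LoAD Calc arm: vignettes, System Usability Scale, confidence.
   - Control arm: vignettes, methods-used question, confidence.

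   The middle step has no content in common between the arms.

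2. **Is confidence the only shared self-rating?** The System Usability Scale goes to one arm. The methods-used question goes to the other arm and is factual. Demographic and prior-use questions are not ratings of the method. Confidence is the only one.

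3. **Can an order effect be separated from the method effect?** Let M_L and M_C be the mean confidence produced by each method, and let S and Q be the shifts (possibly zero) caused by first answering the System Usability Scale or the methods-used question. The observed difference is

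   (M_L + S) − (M_C + Q) = (M_L − M_C) + (S − Q).

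   The first bracket is the quantity wanted. The second vanishes only if the two questionnaires move the rating equally or not at all. Estimating it would need some participants within an arm to rate confidence under a different order, and the text describes none. No counterbalancing is stated, so covariate adjustment cannot recover (S − Q).

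4. **Do the existing safeguards cover it?** Randomisation and stratification by position act before the questionnaires, so they do not balance a difference introduced afterwards. Analyst blinding (Study Design) does not help, because the participant produces the rating. Keeping participants unaware that there are two arms limits comparative demand effects but leaves the order unchanged. The limitations in the Discussion do not mention the point.

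5. **What lies outside its reach?** Overdose rate, underdose rate and calculation time all come from the vignettes, which precede these questions.

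6. **How firm is the order?** The sequence in the text is explicit. Exact adjacency is less certain: Figure 1 is not visible in the copy reviewed, and Inclusion and Exclusion Criteria places a screening question after the vignettes, whereas Consent and Study Sequence and the first-questionnaire box place it before them. Neither point removes the arm-specific questions that the text puts ahead of the rating.

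**The case against.** The strongest reply is that the harm is hypothetical. Nothing in the documents shows an order effect, its direction or its size. Any figure would come from dividing an assumed shift by an assumed SD, so none is offered here. That part of the reply stands.

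It also stands that ten vignettes worked with the method in question are a strong common anchor, and that a short questionnaire may move the rating little. A large difference in confidence would not become meaningless. Confidence is a single item, with no stated hypothesis, no role in the sample size and no named test; the between-arm comparison is inferred from the objective and the general analysis sentence.

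A reader might go further and infer that controls rate themselves after being made to recall makeshift methods. The text does not support this. Groups and Randomization has controls use the method of their usual practice, and naming it is a factual question with no evident pull in either direction. Participants' knowledge of their own method is inherent in an unblinded comparison, and reordering would not change it.

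What survives is narrower: the contexts differ by arm, the difference cannot be adjusted away, and the design does not need it.

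**Conclusion.** The point holds as a minor one. The plan puts the only self-rating common to both arms after questions that differ by arm, so any order effect, of unknown size and direction, would be fully confounded with allocation and could not be removed in analysis. A reader might infer that the confidence comparison is already biased or uninterpretable. The documents do not support that, since they establish only the opportunity for bias.

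The conclusion assumes that the sequence in the text is the one implemented and that confidence will be compared between arms. It concerns one secondary outcome and leaves the primary outcome, underdose rate and calculation time untouched.

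**What to change.** Ask the 1-to-10 confidence item directly after the last vignette, identically in both arms. Then give the System Usability Scale to the LoAD Calc arm and the methods-used question to the control arm. Amend Consent and Study Sequence and Figure 1 to match. If a screening question on prior app use is kept after the vignettes, place it after the confidence item too.

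The cost is small. No participants or items are added, and the Results section says recruitment waits for the protocol's acceptance so that adjustments can still be made. There are two downsides. The study platform is already built and tested, so the changed page order needs a short recheck. One rating item would also precede the System Usability Scale; as that scale is given in one arm only, there is no between-arm comparison of it to disturb.

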**Figure 1 figure1:**
[figure not shown]
Study sequence. LoAD Calc: Local Anesthetics Dose Calculator.

### Outcomes

The primary outcome will be the overall overdose rate, according to the method used. To assess this outcome, the maximum acceptable dose in milligrams, or milliliters, must therefore be established. While this might seem straightforward at first sight, it is actually rather complex. Indeed, although maximum safe doses are calculated in milligrams, anesthetists administer a volume of LA (the concentration of which can vary) rather than a quantity of LA. Therefore, even though toxicity is related to the quantity (in milligrams) of LA administered, it is clinically more relevant to determine the maximum volume (in milliliters) of LA that can be used for a particular patient. Consequently, after applying the rules described in Textbox 1, a quantity in milligrams will be obtained. It will then be converted in milliliters according to the concentration of the LA used in the vignette. This volume will then be rounded to the inferior integer. To be less conservative, 1 mm will be added to this calculated volume, and the total will represent the maximum acceptable volume. An overdose will be considered any dose higher than this maximum acceptable volume or than its corresponding LA quantity in milligrams.

The secondary outcomes will be the overall overdose rate, considering the simulated patient’s ideal weight and the simulated patient’s actual weight, the overdose rate according to each LA studied, and the overall underdose rate. An underdose will be defined as the maximum acceptable volume minus 20% (or its corresponding LA quantity in milligrams), rounded to the inferior integer. This is an empirical choice since anesthetic underdose can only be determined clinically [20,21].

Other secondary outcomes will be the time taken to complete these calculations, the app’s usability, and the physicians’ confidence in using the method they were allocated to. The app’s usability will be evaluated using the System Usability Scale [18]. Provided that the statistical assumptions are met, factors associated with a higher probability of overdose or underdose will also be assessed.

### Statistical Analysis

The sample size calculation and all other statistical analyses will be carried out using Stata (version 17.0 or above). The complete data set will be exported by the webmaster, who will give the study groups codenames before sending the curated data set for statistical analysis. Descriptive statistics will be used to present demographical data. Normality will be assessed graphically, and the Kolmogorov-Smirnov test will be used in cases of doubt. Accordingly, all outcomes will then be computed using either parametric or nonparametric tests. The data acquisition mechanisms will ensure that all data are recorded after each stage. Thus, there should not be any missing data, and there shall be no need for imputation. When LA mixtures are used, participants will be told that 1 anesthetic has already been injected and the dose used has been clearly reported. Thus, they will be asked to determine the maximum safe dose for the second local anesthetic. Multivariable regression will be used to determine an association between specific clinical parameters and the probability of overdose or underdose, provided that all required assumptions are met and that the risk of overfitting is adequately limited. Double-sided *P* values (*P*<.05) will be considered significant.

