### Study Design

This will be a monocentric, parallel-group, randomized controlled trial based on clinical vignettes. The protocol was developed according to the Standard Protocol Items: Recommendations for Interventional Trials (SPIRIT) statement (Multimedia Appendix 1) [14]. Given its design, the investigators will not be blinded as to the intervention. Nevertheless, participants will not be informed that there are 2 different arms and will not be told the exact outcomes studied, even though they will be provided with general information regarding the study. In addition, the data analyst will be blinded as to participant allocation by renaming the groups before sending data for statistical analysis. Randomization will be stratified according to current position (resident vs registrar).

Results will be reported according to the CONSORT-EHEALTH (Consolidated Standards of Reporting Trials of Electronic and Mobile HEalth Applications and onLine TeleHealth) guidelines [15]. Relevant elements of the CHERRIES (Checklist for Reporting Results of Internet E-Surveys) will be included since web-based questionnaires will be used in the course of this study [16].

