### Groups and Randomization

There will be 2 study groups: in the control group, participants will be asked to use the method they usually use in their clinical practice to calculate the maximum safe dose of LA; in the LoAD Calc (experiment) group, participants will be required to use the LoAD Calc app, which will be preinstalled on a standard Geneva University Hospitals (HUG) smartphone (Galaxy XCover 4s; Samsung) running on Android 11.

Stata’s (StataCorp LLC) replicable balanced randomization mechanism will be used to allocate participants to their study group. Textbox 2 contains the code that will be used.

Randomization code.
*set obs #N*

*egen arm = seq(), to(2)*

*set seed #S*

*gen random = uniform()*

*sort random*

Wherein “1” will be the control group, and “2” will be the LoAD Calc group.

Since randomization will be stratified according to participant position (either resident or registrar), 2 seeds (#S) will be used (07022023 and 20230207).

A sample size calculation will be used to determine the total number of observations. It will be rounded up to the nearest ten to enhance the study power and take into account attrition and potential exclusions. The stratified number of observations (#N) will be computed according to the proportion of potential participants belonging to both eligible positions (residents vs registrars).

The method used by the participants allocated to the control group to calculate the maximum safe dose of LA will be recorded. There will be no teaching or introductory intervention for any of the participants before the study, and the participants allocated to the LoAD Calc group will therefore discover the app while answering the first vignette.

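### Renaming the groups does not by itself secure the promised analyst blinding, because some questionnaire items are completed in one arm only

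*Protocol article*

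**What the plan says.** **Blinding.** Study Design states that investigators are not blinded, but that "the data analyst will be blinded as to participant allocation by renaming the groups before sending data for statistical analysis". Statistical Analysis describes the same step in practice: "The complete data set will be exported by the webmaster, who will give the study groups codenames before sending the curated data set". No other masking step is given.

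**Arm-specific items.** Under Consent and Study Sequence, after the vignettes, "the participants allocated to the LoAD Calc group will be asked to complete the French version of the System Usability Scale". In the other arm, "Participants allocated to the control group will then be asked which methods they used to calculate LA doses".

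**Use of those items.** Outcomes makes usability a secondary outcome: "The app’s usability will be evaluated using the System Usability Scale". The control arm's method is to be recorded (Groups and Randomization), but it is not listed among the outcomes.

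**Allocation.** Groups and Randomization prints the Stata code, the arm coding ("Wherein “1” will be the control group, and “2” will be the LoAD Calc group") and the seeds ("2 seeds (#S) will be used (07022023 and 20230207"). Results places recruitment after the protocol has been accepted for publication.

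**The concern.** A codename masks an arm only if nothing else in the file identifies it. Here two items do: a usability scale that can be filled in only by app users, and a question on usual methods that only controls see.

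The analyst still has decisions to take once the data are open. Statistical Analysis leaves three of them until then: the graphical judgement of normality (with a formal test only in doubtful cases), the resulting choice between parametric and nonparametric tests, and whether the assumptions and overfitting risk allow a multivariable regression. The investigators know the arms and the app was developed at the same institution, so a blinded analyst is the main stated safeguard for those decisions. If the trial report claims that safeguard, the plan should deliver it.

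A second, smaller matter is allocation concealment. A published code with published seeds lets anyone with Stata largely rebuild the arm sequence, including investigators who recruit in person.

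**Working it through.** **1. The plan's own figure.** The sample size is not in dispute; it is checked because the stratum sizes below depend on it. Inputs from Results and Statistical Analysis: difference 10%, SD 10%, power 90%, two-sided alpha 0.05. For a two-sample t test with n per arm, the noncentrality is (10/10)/√(2/n) on 2n − 2 degrees of freedom.
- n = 22: power 0.8997, just under 90%.
- n = 23: power 0.9125.

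So 23 per arm, 46 in total, is reproduced. Rounding up to the nearest ten gives 50.

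**2. The blinding statements set side by side.**

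| Item | LoAD Calc arm | Control arm | Listed outcome? |
|---|---|---|---|
| System Usability Scale | completed | not asked | yes, secondary |
| Methods used | not asked | completed | no, recorded only |
| Confidence score | completed | completed | yes, secondary |

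The first two rows identify the arm; the third does not.

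**3. How much one such item reveals.** Two codenames can be matched to two arms in only two ways. A single usability response under one codename settles which way is right. Because every record carries a codename, it settles the arm of every record in the file: up to 50 of 50 at the planned size.

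**4. Is the item expected to reach the analyst?** Usability is an outcome, and the plan says: "The sample size calculation and all other statistical analyses will be carried out using Stata (version 17.0 or above". The scale must therefore be analysed at some point. The article mentions one transfer of data and no second file, later release or separate analyst. It does not say what curation removes.

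**5. The allocation sequence.** Eligible staff are 62 residents and 52 registrars, 114 in all.
- Residents: 50 × 62/114 = 27.2, about 27.
- Registrars: 50 × 52/114 = 22.8, about 23.

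The code numbers places 1, 2, 1, 2 and so on before sorting at random, with 1 as control. It therefore gives 14 control and 13 LoAD Calc places among 27, and 12 and 11 among 23: 26 and 24 overall. With the printed seeds the order of 1s and 2s can be regenerated, apart from three unprinted facts: the final stratum sizes, which seed serves which stratum, and the order of the credentials or envelopes. The code is applied to anonymous generated credentials (Web-Based Study Platform), handed out in opaque sealed envelopes (Consent and Study Sequence).

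**The case against.** The best case against has five parts.

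- **The file sent is not the complete data set.** The complete set is exported, and a curated set is sent. Curation might remove the arm-specific items, and file-transfer details are commonly left to a fuller document. This stands in part: a reader might infer that blinding fails, and the article does not show that. But the article itself names renaming as the means of blinding, and a file stripped of the usability scale would need a second release, which is not described.
- **Not every arm-specific item is an outcome.** This stands. A reader might infer that the analyst needs the methods-used answers because they are an outcome; Outcomes does not list them. The argument rests on the usability scale.
- **Blinding is not the only protection.** This stands. Reference doses are set by three authors in consensus without the app, the overdose limit is arithmetic, and exclusions follow questionnaire answers. The remaining discretion lies in normality, test choice and regression.
- **The seeds do not unblind the analyst.** This stands. A reader might infer from the printed seeds that allocations are already known to analyst or recruiters. The unprinted facts and the opaque envelopes prevent that conclusion. The seeds matter for concealment only, and only if envelopes follow list order, which the article neither states nor excludes.
- **Withholding items may not restore masking.** The reference doses use the same rules as the app, so app-arm answers may cluster at them and give the codename away. This is a fair limit on the remedy. It does not justify leaving a certain identifier in the file.

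**Conclusion.** The stated mechanism does not secure analyst blinding. If the usability scale or the methods-used item is in the file before the between-arm analyses are finished, the codenames are decoded for every participant in it. Whether that happens depends on what curation removes, which is not stated; the supported conclusion is that blinding is unsecured. No bias in the primary result has been shown or quantified, and the sample size is unaffected. The point is worth correcting before recruitment because the analyst's choices are left open until the data are seen and the correction is cheap.

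The printed code and seeds are a separate, minor and conditional weakness of allocation concealment.

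**What to change.** **Analyst blinding.** State in Statistical Analysis that the webmaster sends a comparative file holding codename, position, demographics, vignette answers, times and confidence, without the usability scale, the methods-used item and the usernames. Release the withheld items only after the between-arm analyses are locked. The usability scale has no between-arm comparison, so nothing in the comparative analysis needs it. If staged release is not wanted, drop the claim of a blinded analyst. The cost is one extra export. The trial report should acknowledge that answers clustering at the reference doses may still reveal the app arm.

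**Allocation concealment.** Before recruitment, replace the printed seeds with new ones that the webmaster draws and holds undisclosed until recruitment closes, and shuffle the envelopes within each stratum. The cost is one re-run of the allocation code. Neither change affects participants, outcomes or sample size.

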## Results

The 10 vignettes necessary to carry out the study were successfully created, and the maximum safe doses were determined. These vignettes and the doses were checked and approved by all authors. The 10 vignettes, as well as their English translation, were presented to peer reviewers but are not publicly available to avoid any potential bias. They will nevertheless be published along with the results paper.

The sample size calculation was performed using Stata (version 17.0). It showed that 46 participants (23 in each group) would be needed to detect a 10% difference with a power of 90%, taking into account an SD of 10%. In line with the above methods, a total of 50 anesthesiologists should therefore be recruited. Since there are 62 residents and 52 registrars in the HUG Anesthesiology Department, a participation rate of 44% (50/114) will be necessary. This participation rate seems achievable with the aforementioned recruitment procedure. If this rate cannot be achieved, other Swiss University hospitals will be contacted, and similar recruitment procedures will be carried out to obtain the required sample size.

The study platform has been successfully created and tested by all coauthors [22]. The data extraction mechanisms have also been successfully checked.

The recruitment will take place once this study protocol has been reviewed and accepted for publication to allow for any necessary adjustments before study inception. The current version of the protocol is 0.9 (October 10, 2023). The published version will be 1.0.

It should be possible to start recruitment during the winter of 2023. This would allow data analysis to take place in spring 2024, and results should be submitted for publication in an international peer-reviewed journal by the end of the same year.

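### A normality check on the data chooses the primary test, although the trial is sized on a mean difference and non-normality is known in advance; fix one mean-difference analysis that includes position

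*Protocol article*

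**What the plan says.** The Outcomes section defines the primary endpoint: "The primary outcome will be the overall overdose rate, according to the method used". The Statistical Analysis section then gives the rule for choosing a test: "Normality will be assessed graphically, and the Kolmogorov-Smirnov test will be used in cases of doubt". It continues: "Accordingly, all outcomes will then be computed using either parametric or nonparametric tests". Significance is two-sided at 5% ("Double-sided *P* values (*P*<.05) will be considered significant"). The section names no test or effect measure for the primary outcome. It does not say what counts as doubt, or whether normality is judged by arm or on pooled data.

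The Results section gives the calculated size as "46 participants (23 in each group"). The assumptions behind that number are stated there too, with the SD in percentage points: "would be needed to detect a 10% difference with a power of 90%, taking into account an SD of 10". The target is then raised: "a total of 50 anesthesiologists should therefore be recruited".

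The Study Design section states: "Randomization will be stratified according to current position (resident vs registrar"). The Statistical Analysis section does not mention position. The only regression it describes looks for clinical parameters associated with overdose or underdose, and it is conditional on assumptions being met.

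**The concern.** A rule that waits for the data is useful only if the data can tell the analyst something not already known. Here they cannot. A rate out of ten vignettes is discrete and bounded, and it will pile up at zero if the app works well.

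The two branches of the rule also answer different questions. A t test compares mean overdose percentages, which is what the sample size assumes. A rank test asks whether values in one arm tend to exceed those in the other, and gives no difference in percentage points. So both the test and the quantity reported as the main result stay open until the data are seen.

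A smaller matter goes with this. Allocation is stratified by position. If residents and registrars differ in overdose rate, a comparison that leaves position out has a standard error that is too large. Since the primary analysis needs to be written down anyway, position should be settled in the same sentence.

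**Working it through.** **1. The plan's own figure.** Inputs from the Results and Statistical Analysis sections: difference 10 points, SD 10 points, power 90%, two-sided 5%. The normal approximation gives n per arm = 2(1.960 + 1.282)² × 10²/10² = 21.0, so 22. The noncentral t calculation, with noncentrality √(n/2) and 2n − 2 degrees of freedom, gives:
- 89.97% power at 22 per arm;
- 91.25% at 23 per arm;
- 93.37% at 25 per arm.

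The smallest n reaching 90% is 23, so the stated 46 is reproduced. It is the figure for an unadjusted two-sample t test, which means the trial is designed for a difference in means.

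**2. Possible values.** Ten vignettes give 0, 10, …, 100%, which is 11 values.

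**3. What the check would report.** The overdose rates here are assumed, because the documents give none. The ordinary Kolmogorov-Smirnov test was applied to one arm of 25, with mean and SD estimated from the sample and binomial counts out of 10:

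| Data | Rejects normality |
|---|---|
| Truly normal | 0% |
| Overdose rate 5% | about 97% |
| Overdose rate 10% | about 39% |
| Overdose rate 20-40% | about 3-10% |

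None of the binomial rows is normal, yet the verdict runs from almost always to almost never. The version of the test matters as well. With the Lilliefors correction on pooled residuals and beta-binomial counts, overdose rates of 5-30% sent 62-100% of runs to the nonparametric branch. The protocol does not say which version applies.

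**4. Does the branch matter?** Simulated with 25 per arm and a true 10-point difference:
- Beta-binomial counts, 2,000 runs per scenario: the t test and Mann-Whitney disagreed on significance in 6.5-8.7% of runs. At 15% vs 5%, for example, power was 87% and 96% respectively.
- Plain binomial counts: they disagreed in 2-6% of runs.
- Over all the assumed settings examined: roughly 2-11%.

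With no true difference they disagreed in 1-2% of runs. When position had no effect, the choose-after-checking rule had type I error of about 5%.

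**5. Position.** The department has 62 residents and 52 registrars, so p = 62/114 = 0.544 and p(1 − p) = 0.248. A gap of g points between positions explains 0.248g² of the total variance of 100. For g = 5 the SD within position is √(100 − 6.2) = 9.68, and for g = 10 it is √(100 − 24.8) = 8.67. The documents give no value for g, so the table shows an assumed range, with 25 per arm and total SD 10:

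| Gap | Adjusted power at 10 points | Unadjusted type I error |
|---|---|---|
| 0 | 93.4% | 5% |
| 5 | 94.7% | 4.4% |
| 8 | 96.4% | 3.2-3.3% |
| 10 | 97.9% | 2.3-2.4% |

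For a 10-point gap, the power gained over the unadjusted test is about 1-4 points. The spread comes from how the odd-sized strata (about 27 and 23) fall between the arms. With 14/13 and 12/11 the gain is 2.4 points. When the uneven split works against the treatment difference it is 3.8 points (94.0% to 97.8%), and when it works in favour it is about 1 point. With no gap there is no gain.

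**6. Sample size under either branch.** On normal data a rank test needs about 23/0.955 = 24.1 per arm, within the target of 25. Adjusting for position needs no more participants.

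**The case against.** The best defence is that little harm has been shown. Choosing after checking did not raise the false-positive rate, and the two tests agree in the large majority of runs. The analyst works with renamed groups, so the test cannot easily be picked to favour the app. The Kolmogorov-Smirnov test is only a fallback after graphical assessment, and an outcome stacked at zero would be seen by eye. All of this stands, and it limits how serious the point is. It does not name the primary test or the quantity to be estimated, and blinding to group names does not define when there is doubt.

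A reader might infer that the pretest produces false positives. The simulations do not support that.

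A reader might also infer that the plan excludes position from the analysis. No sentence says so. The article condenses a fuller plan, and covariate adjustment is commonly set out in an analysis plan, which is not shown here. That position goes unmentioned is a reason to include it when the analysis is fixed; it does not show that the planned analysis is wrong.

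Finally, a gap of 8-10 points between positions is as large as, or nearly as large as, the treatment effect the trial is designed to detect. In the normal-outcome calculations with total SD 10, the unadjusted test stays above the planned 90% power at the design effect for every gap tried, and its error is only conservative.

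**Conclusion.** The point holds in a limited form. The protocol states a rule that leaves the primary test and its estimand open until the data are seen. It does so for an outcome whose non-normality is already known, in a trial sized on a mean difference. The consequence is a chance of roughly 2-11%, under assumed overdose rates and a true 10-point difference, that the branch taken decides significance. There is also the prospect of a main result that is not a difference in percentage points. No inflation of type I error was found, and the sample size is not in question.

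The benefit of including position depends on a gap between residents and registrars that the documents do not give. It is nil with no gap. At the designed effect it is about 1-4 points of power for an assumed 10-point gap. Without adjustment, type I error would be about 2-3% instead of 5% for an assumed 8-10 point gap. This is a worthwhile improvement at almost no cost, not an error that invalidates the design.

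**What to change.** For the primary outcome, remove the normality check and state one analysis: linear regression of each participant's overdose percentage on allocated arm and position, with heteroscedasticity-robust standard errors because the spread is likely to differ between arms. Report the adjusted difference in percentage points, with its 95% CI and P value from that same model so that the two cannot conflict. Name a rank test or a permutation test stratified by position as a sensitivity analysis.

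The cost is a few lines in the protocol or analysis plan. Stata, already the chosen software, fits this model directly. No new data or participants are needed, since position is already collected and used for allocation. The Results section says recruitment waits for review of the protocol so that adjustments can be made, which leaves room for this change before the first participant.
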